### Sample Size

As this is a feasibility study that does not intend to assess effectiveness, demonstration of differences between groups is not a key objective. We are interested in the parameters of the outcome measurements in order to assess the utility of each outcome measure and enable sample size estimation for a future definitive trial. Thus, the focus is on the acceptability and usability of the MIRA Rehab program, and we shall use the results to guide the design of a potential definitive RCT [25]. As recommended by Hooper [26], the total number of participants was approximately 30. Anticipating an attrition rate of 20% for feasibility study, we recruited 19 persons in each arm to recruit approximately 15 older participants in each group [26].

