### Randomization

Randomization to the intervention or control group was undertaken by a separate member of the research team after baseline measurements were taken. We used an equal allocation ratio of 1:1. Taking into account the allocation ratio for 2 groups, the block size can be 2, 4, or 6. Randomization was undertaken by permuted blocks of size 2-6, using the Sealed Envelope randomization service [27].

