### Statistical Analysis

Statistical analysis is currently underway. The baseline characteristics of the participants will be reported using mean and SD values for normally distributed variables and median and IQR values ranges for nonnormally distributed variables. Analysis is being conducted using SPSS (version 27.0; IBM Corp) [40]. Continuous data, such as retention and recruitment rates, will be identified as percentages. Both groups will be compared at baseline with respect to their continuous and categorical variables using independent samples *t* tests and the Fisher exact test, respectively. Changes in balance and function will be compared between the intervention group and the control group from baseline (week 0) to follow-up (weeks 6 and 12). Inferential findings will be interpreted cautiously, as the feasibility analysis is underpowered for detecting significant effects. Distribution of data will be explored as normal or skewed. For normal distributions, mean and SDs will be used. For skewed distributions, minima, maxima, medians, and quartiles will also be used. We will report 95% CIs for unadjusted differences in mean outcome scores between the groups. Changes in mean scores over 3 time points (weeks 0, 6, and 12) as well as changes in average scores for each result will be recorded using repeated measures ANOVA. The effect size for the differences between the intervention and control groups and the variations within the intervention group will be estimated. Other relevant models will be used in the case of nonnormally distributed data. The findings will be used to calculate the optimum sample size (number of participants) for determining a statistically significant true effect in preparation of a future definitive RCT. Both intention-to-treat and per-protocol analyses will be undertaken. This feasibility RCT is a hypothesis-generating study for preparing and conducting additional analyses not identified in this protocol paper.

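### Repeated measures ANOVA over weeks 0, 6 and 12 keeps only men seen at all three visits and makes no covariate use of baseline; a baseline-adjusted mixed model fits the stated intention-to-treat analysis better

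*Protocol article*

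**What the plan says.** The Statistical Analysis section describes the longitudinal analysis as "Changes in mean scores over 3 time points (weeks 0, 6, and 12" and continues that "changes in average scores for each result will be recorded using repeated measures ANOVA". The software is SPSS 27; the procedure is not named. The same section adds three related statements:

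- Change scores for the balance and function measures "will be compared between the intervention group and the control group from baseline (week 0) to follow-up (weeks 6 and 12".
- "We will report 95% CIs for unadjusted differences in mean outcome scores between the groups".
- "Both intention-to-treat and per-protocol analyses will be undertaken".

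It also says that group effect sizes will be estimated and the findings used to calculate the sample size of a definitive trial. No missing-data method, all-available-data model or baseline covariate is named.

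The Sample Size section, "Anticipating an attrition rate of 20% for feasibility study", recruits 19 men per arm to leave about 15. The Randomization section says that allocation was "undertaken by a separate member of the research team after baseline measurements were taken".

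**The concern.** Two features of the named method work against the plan's own aims.

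First, classical repeated measures ANOVA needs a value at every level of the time factor. A man assessed at weeks 0 and 6 but not at week 12 is removed entirely, although he has a valid follow-up outcome. The result is a completer analysis, which blurs the distinction between the intention-to-treat and per-protocol analyses that the plan wants to report.

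Second, week 0 was measured before allocation. It carries no treatment effect, but it does carry information about each man's later scores. As one more outcome level it is not used to remove chance imbalance between two small arms, and the planned confidence intervals are explicitly unadjusted.

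The stake is the quality of the means, SDs and effect sizes handed to the definitive trial, not a significance test.

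**Working it through.** **The plan's own figure.** 15 / (1 − 0.20) = 18.75, rounded up to 19 per arm, or 38 in total. This reproduces.

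**Participants lost to complete-case analysis.** 38 × 0.80 = 30.4 retained and 38 × 0.20 = 7.6, so about 8 lost. If k of these 8 had a week 6 assessment before leaving, an all-available-data model keeps about 30 + k men. The article does not say when attrition is expected, so k can be anything from 0 to 8.

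**Precision from baseline.** The documents give no SDs or correlations. Assumptions: SD 1 at each visit, a common correlation ρ between visits, and n = 15 per arm. The quantity is the group difference in the mean of weeks 6 and 12, with SE = √(2v/n) and

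- unadjusted: v = (1 + ρ)/2
- change from baseline: v = (1 + ρ)/2 + 1 − 2ρ
- baseline as covariate: v = (1 + ρ)/2 − ρ²

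| ρ | SE unadjusted | SE change | SE covariate | Reduction vs unadjusted | Reduction vs change |
|---|---|---|---|---|---|
| 0.5 | 0.316 | 0.316 | 0.258 | 18% | 18% |
| 0.7 | 0.337 | 0.245 | 0.219 | 35% | 11% |
| 0.8 | 0.346 | 0.200 | 0.186 | 46% | 7% |

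**What each ANOVA term estimates.** Let the true difference be 0 at week 0 and d at both follow-ups.

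- Group main effect: (0 + d + d)/3 = 0.67d. For an assumed d = 0.5 SD this is 0.33 SD. If the effect were present only at week 6, it would be d/3.
- Group-by-time, as mean follow-up minus baseline: (d + d)/2 − 0 = d. There is no dilution, and the same holds for change from baseline.

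**Illustrative power** (d = 0.5 SD at both follow-ups, 15 per arm, ρ = 0.5 / 0.7 / 0.8; the first two rows from simulation, 4,000 runs per setting, the others analytic):

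- group main effect: 19% / 17% / 17%
- group-by-time: 26% / 42% / 59%
- baseline-adjusted mean of weeks 6 and 12: 46% / 60% / 74%
- baseline-adjusted difference at a single visit: 33% / 46% / 60%

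**The case against.** The strongest reply has four parts.

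1. **Intention-to-treat.** Imputation before the ANOVA would reconcile the method with the analysis set, and a condensed article may leave that detail to a fuller plan that is not shown. This stands: the mismatch is conditional, and silence on imputation is not itself the point. What remains is that the one named longitudinal method is a complete-case method unless something is added to it.

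2. **Dilution.** A reader might infer that the treatment effect will be reported at two-thirds of its size. Using n = 2(1.960 + 0.842)²/d², the definitive trial would then be sized at 142 per arm (d = 0.33) and not 63 (d = 0.5). The documents do not support this. The article never names the group main effect as the treatment contrast, and the contrast it does describe, change from baseline compared between groups, is undiluted.

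3. **Other estimates exist.** The unadjusted confidence intervals and the change comparisons could be computed visit by visit from whoever attended. True, but neither uses baseline as a covariate, so the precision loss remains, smaller for change scores than for raw differences.

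4. **The remedy is limited.** A man with no follow-up value is not recovered. The power advantage is also modest when like is compared with like: single-visit adjusted power (33% to 60%) is close to that of the group-by-time test (26% to 59%). Both observations are right, and the case for change does not rest on power.

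A reader might also infer that completer estimates will be biased because frailer residents leave. That is possible in a care home, but nothing in the article shows it.

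**Conclusion.** The point holds in a limited form. Repeated measures ANOVA over three visits would, without imputation, exclude up to about 8 of 38 randomised men at the plan's own 20% attrition, which does not fit its intention-to-treat label. How many of them a better model would retain depends on when they left.

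It also makes no covariate use of baseline. Under the assumed correlations of 0.5 to 0.8 and equal SDs, adjustment would reduce the standard error by 7% to 18% against change scores and by 18% to 46% against unadjusted differences. The effect sizes, correlations and power figures are assumptions and only illustrative.

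This is a worthwhile, free improvement. It is not a must-fix: the article says the study does not assess effectiveness, sets no power target, and makes recruitment, attrition, adherence and acceptability its main products.

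**What to change.** Replace the repeated measures ANOVA with a linear mixed model (SPSS MIXED, REML) as follows:

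- **Outcomes:** weeks 6 and 12 only.
- **Fixed effects:** group, visit, group-by-visit and the baseline value, with the within-person correlation between the two visits modelled.
- **Analysis set:** every randomised man with at least one post-baseline value, in his allocated arm.
- **Reporting:** baseline-adjusted group differences at week 6 and at week 12, each with a 95% CI, and the number missing at each visit by arm.

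Men with no follow-up value should be counted and described, because the model does not bring them back. If the ANOVA is kept, state the imputation method and name group-by-time or change from baseline, not the group main effect, as the treatment contrast.

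The cost is a few sentences and a different procedure in the same software, with no new data. Because the article describes analysis as under way, the report should say whether the change was made before results by group were seen.

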### Ethics Approval and Research Governance

This study has been approved by the University of Manchester Research Ethics Committee (reference number 2021-11191-20154). To enable access to participants at the social care home for older individuals, permission has also been obtained from the local institution in Saudi Arabia that is responsible for the investigator’s research and training. This study adheres to the tenets of the Helsinki Declaration. Prior to participation in the study, all participants were given a written informed consent form.

## Results

This study is funded by Saudi Arabian cultural mission as part of a PhD project. Data collection started in November 2021 and ended in March 2022. The study is currently in the feasibility data collection stage, which commenced in May 2022. Additional qualitative data collection and analysis are ongoing and will be completed in January 2023.

## Discussion

### Expected Findings

This is the first feasibility RCT of MIRA Rehab Exergames in a residential care center for older adults (aged 60 years and older) in Saudi Arabia. While other researchers have studied various Exergame technologies, they have not examined purposely designed Exergame technology for older adults. Exergames for fall prevention were administered for over 6 weeks with a 6-week follow-up and compared to a control group receiving an exercise educational package. The study tested the feasibility of conducting an RCT of this novel technology in a new cultural context. This feasibility study protocol is intended to provide as much information as possible for a future randomized controlled trial. The study investigates the delivery of MIRA Rehab Exergames in the context of Saudi Arabia and included a small sample, with one site researcher. The findings may also inform whether Arabic and Saudi adaptations should be added to provide an adapted Exergame system that reflects cultural considerations. It will be critical for future research to examine how Exergames affect larger populations. Researchers should also carry out longitudinal investigations to assess changes in fall rates. Additionally, researchers should evaluate optimal exercise doses to inform potential future implementation.

### Conclusions

This study will contribute to our understanding of how to recruit in this specific population and provide information to inform the design of a future RCT. MIRA Rehab Exergames may be a feasible and practical exercise intervention for enhancing the functional performance of older adults and to improve physical activity levels. Health care providers, such as physiotherapists and rehabilitation teams, may include Exergames such as the MIRA Rehab programs as part of a comprehensive physical therapy intervention for older adults living in care homes or similar settings.

## Appendix

Multimedia Appendix 1 CONSORT 2010 checklist for reporting pilot or feasibility trials.

Multimedia Appendix 2 The Arabic version of chair based training (CBT) provided by Later Life Training.

Multimedia Appendix 3 The English version of chair based training (CBT) provided by Later Life Training.

Multimedia Appendix 4 Participants’ observations during data collection.

## Abbreviations

FaME: Falls Management Exercise
RCT: randomized controlled trial
